#### Settings and eligibility

Settings are eligible if trained and experienced trainers provide the IMR programme. Consumers who are referred to the IMR programme by their clinician will be eligible to participate. Consumers that meet the following criteria will be included: above 18 years of age, capable of giving informed consent, and meeting the SMI criteria: having a diagnoses of schizophrenia, schizo-affective disorder, bipolar disorder, or major depression, with a duration of one year since onset, and a disability that is sufficiently severe to cause serious impairment of functioning in family responsibilities, occupation, and accommodation [29].

#### Data collection

At baseline we will collect the participant characteristics: age, gender, living situation, social economic status, diagnosis, time since diagnosis, previous treatment, latest relapse, relapse frequencies in the past, and computer/internet availability and literacy. Also at baseline we collect the trainer characteristics: profession, highest education, gender, age, years of experience in mental health, and the number of executed IMR programmes in the past.

At baseline and at twelve months the trainers will be interviewed and rated according to the IMR Fidelity Scale [30] to assure that the IMR programme is executed as it is meant to be.

To measure the effect we will examine the following parameters at baseline, six, and twelve months: illness management, recovery, psychiatric symptoms severity, self-management, quality of life, and general health. Respectively, we use the following measurements: (1) the clinician and consumer version of the Illness Management and Recovery Scales [31, 32], (2) the Mental Health Recovery Measure [33, 34], (3) the Brief Symptom Inventory [35, 36], (4) the Patient Activation Measure [37, 38], (5) the Manchester Short Assessment of Quality of Life [39], and (6) the RAND 36-Item Health Survey [40].

At 12 months we will gather login data on the frequency of participants’ use of the website of the e-IMR intervention. When participants and trainers completed the 12-month questionnaires, we will interview them qualitatively about the added value of the e-IMR intervention, the actual use and continued participation, or dropping out.

#### Analyses

Quantitative analyses will be executed according to the intention to treat principle. Multilevel regression with a random setting effect and repeated measures will be used to explore the effectiveness of the e-IMR intervention. Baseline measures and participants’ characteristics will be added as covariates. The relevance of the frequency of participants’ use of e-IMR intervention, consumer characteristics, trainer characteristics, and IMR Fidelity Scale ratings will be explored by performing sub-group analyses.

The process of interviewing and analysing the qualitative data will be guided by the modified method of Stevick–Colaizzi–Keen [41].

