### Step 6: Planning for evaluation

The sixth and last step aimed to develop an evaluation plan to determine whether the e-IMR intervention contributes to the recovery process of consumers with SMI and matches the consumers’ preferences. For this purpose we studied the Medical Research Council guidance [26].

As a result, we decided to test the e-IMR intervention in an exploratory cluster randomized controlled trial with a twelve-month follow-up from baseline. This trial will not be powered as it will aim to (1) explore the potential effectiveness and effect-size, (2) to identify outcome measures that most likely capture consumers’ potential benefits of the e-IMR intervention, (3) to explore the actual use and added value, and (4) to evaluate continued participation or dropping out of the e-IMR intervention.

Participants in the experimental condition will receive the e-IMR interventions containing the use of the hard copy textbook and the programme components described in step 4. Participants in the control condition will receive the IMR programme only using the hard copy textbook. Both conditions will be provided in individual or group sessions. All participants will also receive care consisting of extensive in- and/or outpatient psychiatric services including case management and guideline-based psychiatric treatments.

Before randomization, we stratified institutions within types (outpatients/inpatients clinics). Due to risk of contamination, units that could contaminate each other were combined in one cluster. Because of high attrition rates in the IMR programme [27] and e-health [28] we need 50 participants in both conditions.

The inclusion period has been closed in October 2015. The follow-up will last until the end of October 2016 followed by the results at the end of December 2016.

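### Randomisation was stratified by inpatient/outpatient type, but the covariates stated for the multilevel model do not include type, so standard errors will be too large if type predicts outcome

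*Protocol article*

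**What the plan says.** In Step 6: Planning for evaluation, the protocol article describes the allocation: "Before randomization, we stratified institutions within types (outpatients/inpatients clinics"). Clusters were formed so that "units that could contaminate each other were combined in one cluster". Type is thus a property of the institution, fixed before randomisation.

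Under Analyses, the model is given as: "Multilevel regression with a random setting effect and repeated measures will be used to explore the effectiveness of the e-IMR intervention". The covariate sentence follows: "Baseline measures and participants’ characteristics will be added as covariates".

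The characteristics are listed under Data collection: "At baseline we will collect the participant characteristics: age, gender, living situation, social economic status, diagnosis, time since diagnosis, previous treatment, latest relapse". The list ends with past relapse frequency and computer or internet availability and literacy. Inpatient or outpatient status is not on it. Type is also absent from the factors named for the sub-group analyses.

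On size, Step 6 says "Because of high attrition rates in the IMR programme [27] and e-health [28] we need 50 participants in both conditions" and, of the design, "This trial will not be powered as it will aim to" explore several questions, the first being potential effectiveness and effect size.

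**The concern.** A factor used to stratify the randomisation normally belongs in the analysis model. Stratification makes the arms alike on type, so the true sampling variation of the treatment effect no longer contains the inpatient/outpatient difference. A model without type does not know this. It sees settings that differ and attributes the whole difference to random setting variance. That variance feeds the standard error of a cluster-level treatment effect. The random setting effect is no substitute for the stratum term, because it treats a known difference as unexplained noise.

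At stake is the precision that the trial reports. Its products are an estimated effect size and a choice of outcome measures for later work. Intervals that are wider than they need be could make a promising measure look uninformative. The setting variance would also be overstated for anyone who uses it to plan the next trial.

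**Working it through.** **Inputs from the protocol article.** Stratification by type; cluster randomisation; random setting effect; 50 participants per condition, read as 100 in total. There is no stated figure to reproduce: the article gives no power, ICC, SD, number of clusters or outcome difference by type.

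**Assumed inputs.** *K* clusters of equal size per arm, half of them inpatient; ICC 0.03 to 0.05; outcome SD 1; *d* = difference in outcome between types, in SD, that remains after the other covariates; one time point.

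**Formula.** With half the clusters of each type, the type difference adds *d*²/4 to the between-cluster variance if type is left out.

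- Variance reported without type: 2 × [(ICC + *d*²/4)/*K* + (1 − ICC)/50]
- Variance with type: 2 × [ICC/*K* + (1 − ICC)/50]
- Inflation of the standard error: square root of the ratio, minus 1

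The factor 2 cancels. For *K* = 8, ICC 0.05 and *d* = 0.3: (0.05 + 0.0225)/8 + 0.95/50 = 0.02806, against 0.05/8 + 0.95/50 = 0.02525. The ratio is 1.111, its root 1.054, and the inflation 5.4%.

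| Clusters per arm (total) | ICC | *d* = 0 | *d* = 0.3 | *d* = 0.5 |
|---|---|---|---|---|
| 8 (16) | 0.05 | 0% | 5.4% | 14.4% |
| 5 (10) | 0.03 | 0% | 8.5% | 22.2% |
| 4 (8) | 0.05 | 0% | 8.6% | 22.3% |
| 4 (8) | 0.03 | 0% | 10.0% | 25.7% |

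Five clusters per arm cannot split evenly. With a 2:3 split, *d*²/4 becomes 0.24 *d*² and that row falls to 8.2% and 21.3%.

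At *d* = 0.5 a nominal 5% normal test has an actual level of about 2.5% (1.96 × 1.144 = 2.24) for 16 clusters and 1.7% (1.96 × 1.222 = 2.39) for 10.

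**Simulation.** 100 participants; 8, 12 or 16 clusters in total, half inpatient, randomised 1:1 within type; ICC 0.05; no treatment effect; random-intercept REML with and without type; 1,500 runs per scenario. Mean model standard errors with equal cluster sizes:

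| Total clusters | *d* = 0.3: without / with type | Inflation | *d* = 0.6: without / with type | Inflation |
|---|---|---|---|---|
| 8 | 0.278 / 0.254 | 9% | 0.342 / 0.255 | 34% |
| 12 | 0.256 / 0.241 | 6% | 0.299 / 0.240 | 25% |
| 16 | 0.242 / 0.232 | 4% | 0.275 / 0.229 | 20% |

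Unequal cluster sizes give 5% to 8% at 0.3 SD and 20% to 35% at 0.6 SD. With *d* = 0 and 8 equal clusters the standard errors are 0.254 without and 0.255 with type, so including type costs almost nothing when it is not needed. For *d* of 0.3 or more, up to the 0.9 SD tried, type I error ran from 0.1% to 4.0% without type and from 1.3% to 4.7% with it.

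**Is the estimate itself affected?** With equal cluster sizes and an even number of clusters per type, imbalance on type was zero and the summary results for the estimate (mean and sampling SD) were the same under both models. With unequal sizes, the between-arm difference in inpatient share had an SD of 0.15 to 0.22. Leaving type out then raised the true sampling SD by at most about 5% (for example 0.292 against 0.278 with 8 clusters and *d* = 0.9). Mean estimates stayed within 0.015 of zero under both models.

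**The case against.** The strongest objection is that the Analyses section is a few sentences in a condensed article. The covariate sentence names two classes of covariate and does not say that nothing else enters. An itemised list may sit in a fuller document that is not shown. That stands as a limit: the text does not show a decision to exclude type. But the article does not defer the matter. It names the stratification factor and it names the covariates, and the two do not match.

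A second objection concerns size, and most of it stands. Every input except the 50 per arm and the stratification is assumed. What counts is the difference left after baseline scores, living situation, diagnosis, previous treatment and relapse history, which plausibly absorb part of any type effect. The half-and-half mix is favourable to the concern: with 20% of clusters of one type, *d*²/4 becomes 0.16 *d*², and the 5.4% figure falls to 3.5% ((0.05 + 0.0144)/8 + 0.019 = 0.02705; 0.02705/0.02525 = 1.071; root 1.035).

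A third is that the trial is exploratory and unpowered, and that the error is on the safe side. This is true: it does not produce false positives. It lowers the urgency, but interval width still matters when effect size is what the trial sets out to explore.

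A reader might go further and infer that leaving type out biases the effect, for instance that a 40% against 60% inpatient share with a 0.5 SD difference would move it by 0.20 × 0.5 = 0.10 SD. The documents do not support that. The split is invented, the arithmetic belongs to a simple participant-weighted comparison rather than a model with a random setting effect, and stratifying by type is what largely prevents such imbalance.

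**Conclusion.** The point holds as a matter of precision. The stated covariates leave out the factor on which randomisation was stratified, and to the extent that type predicts outcome after adjustment, reported standard errors are too large, intervals too wide and tests conservative.

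With about half the clusters inpatient, an ICC of 0.03 to 0.05 and 50 per arm, the inflation is roughly 4% to 9% at a residual difference of 0.3 SD and 14% to 22% at 0.5 SD. The second range is for 10 to 16 clusters in total; the most adverse corner tried, 8 clusters with an ICC of 0.03, gives 10% and 26%. It is nil if no difference remains. Because baseline adjustment will absorb some of the difference, the lower end is the safer guide. The mismatch in the text is certain; the size of the harm is not known from the documents.

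There is no systematic bias. Residual imbalance on type can come from unequal cluster sizes or an odd number of clusters within a type, and in the unequal-size scenarios simulated its effect was minor. This is a modest weakness in an exploratory trial, worth correcting because the correction is so cheap.

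**What to change.** Add institution type (outpatient or inpatient), coded as it was used in the randomisation, as a fixed effect in every multilevel model. Keep the random setting effect and the baseline value of the outcome being analysed alongside it, and name the term in the analysis text.

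Type was known before randomisation, so no new data are needed. The cost is one between-cluster degree of freedom: with 8 clusters in total, for example, 5 instead of 6 when the degrees of freedom are counted as clusters minus cluster-level parameters (8 − 3 against 8 − 2).

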### Step 5: Planning program adoption and implementation

The fifth Intervention Mapping step aimed to prepare the adoption and implementation of the e-IMR intervention in the Netherlands. For this purpose we studied the literature on telemedicine for consumers with SMI to identify implementation barriers, and we conducted structured interviews with 52 Dutch consumers with SMI regarding the use of computers and the Internet.

As a result, we decided to implement the e-IMR intervention in institutions that already provide the IMR programme. These institutes are assembled in the Dutch IMR network. Saxion, University of Applied Sciences supports this network and educates trainers to carry out the IMR programme. This network facilitates the implementation and provides trainers that will be able to execute the e-IMR intervention after being instructed how to use the applications of the e-IMR intervention.

Implementation could not only be hindered by cognitive impairments and lower technology experience of consumers with SMI [7], but also by not having access to a computer. The results of the structured interviews showed that approximately 40 % of consumers with SMI had no computer, mostly because of financial problems. Therefore, we will assess the consumers’ computer skills before they enter the e-IMR intervention. When necessary we will help the consumer to search for a place where he or she can use a computer and support him or her to learn to use the website of the e-IMR intervention.

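### Frequency of e-IMR use is listed for sub-group analysis, but it arises after randomisation and in one arm only, so selection cannot be separated from any effect of use

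*Protocol article*

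**What the plan says.** In the protocol article, the Analyses section first sets the main approach: "Quantitative analyses will be executed according to the intention to treat principle", with a multilevel repeated-measures model and with baseline measures and participant characteristics as covariates. It then turns to "The relevance of the frequency of participants’ use of e-IMR intervention" and assigns it to sub-group analysis, together with the characteristics of consumers and of trainers and the fidelity ratings. Four kinds of variable thus share one method.

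The Data collection section says how use is obtained: "At 12 months we will gather login data on the frequency of participants’ use of the website of the e-IMR intervention". Outcomes are collected at baseline, six and twelve months. For fidelity it says: "At baseline and at twelve months the trainers will be interviewed and rated according to the IMR Fidelity Scale".

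Step 6 defines the arms. The experimental arm receives the textbook together with the website components set out under Step 4. On the control side: "Participants in the control condition will receive the IMR programme only using the hard copy textbook".

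Step 6 also calls the trial exploratory and unpowered. Its aims include exploring potential effectiveness and effect size (aim 1), actual use and added value (aim 3), and continued participation or drop-out (aim 4).

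**The concern.** A sub-group analysis of a randomised trial asks whether the difference between arms varies across levels of a characteristic that participants in both arms have, and that allocation could not have changed. Consumer and trainer characteristics recorded at baseline meet that condition. Frequency of website use fails it twice: it accumulates after allocation, and it has no counterpart among controls.

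If the stated method is followed, the output is a difference between self-selected groups presented under the name of a sub-group effect. A reader could take it as evidence that the e-health components work in those who use them. That bears on aims 1 and 3, which concern potential effect size and the value added by the e-health part.

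**Working it through.** The plan gives no figure for this analysis, so there is nothing to reproduce. The check is first a comparison of sections, then an illustration with an assumed input.

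**1. Timing.** Use is a count of logins gathered at 12 months (Data collection), and outcomes are measured at six and twelve months. Use and outcome therefore build up over the same period, and each could influence the other.

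**2. Which arms have the variable.** Step 6 gives website components to the experimental arm and the textbook alone to controls. Write A for arm and U for use. A sub-group effect at level u is E[Y | A=1, U=u] − E[Y | A=0, U=u]. The second term does not exist, so neither this difference nor an A×U interaction can be estimated. What remains is high against low users within the e-IMR arm, or selected users against all controls. Neither is a randomised comparison.

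**3. Sources of selection that the article itself describes.**
- Step 5: "Implementation could not only be hindered by cognitive impairments and lower technology experience of consumers with SMI", and about 40% of those interviewed had no computer, mostly for financial reasons. These factors could plausibly relate to outcome as well as to use.
- Step 4: goal follow-up begins at the end of module 1, coping follow-up at the end of module 2, and weekly symptom e-mails after module 2. Someone who leaves early has less opportunity to log in, so total use is partly a record of retention in the face-to-face programme, which controls also receive.
- Step 6 expects high attrition both in the IMR programme and in e-health.

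**4. Illustration of size.** Let use Z and outcome Y be standardised, with no true effect of e-IMR and a correlation r that arises from prognosis alone. The documents give no value of r; 0.2 to 0.5 is an assumption. It should be read as the residual correlation after any baseline adjustment.

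For normal Z split at its median, E[Z | upper half] = 0.3989 / 0.5 = 0.798. Hence:
- upper half of users minus all controls = 0.798r
- upper half minus lower half of users = 2 × 0.798r = 1.596r

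At r = 0.2 these are 0.16 and 0.32 SD. At r = 0.5 they are 0.40 and 0.80 SD.

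A simulation checked the formulas and showed how often a nominal 5% test would reject. It used 20,000 trials per row, 50 per arm, use split at the median (25 and 25), true effect zero, and no clustering or attrition:

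| Assumed r | High − controls (SD) | Rejects | High − low users (SD) | Rejects |
|---|---|---|---|---|
| 0 | 0.00 | 5% | 0.00 | 5% |
| 0.1 | 0.08 | 6% | 0.16 | 8% |
| 0.2 | 0.15 | 10% | 0.31 | 20% |
| 0.3 | 0.23 | 16% | 0.47 | 39% |
| 0.4 | 0.32 | 26% | 0.63 | 63% |
| 0.5 | 0.39 | 38% | 0.78 | 84% |

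The simulated differences lie slightly below the formula because the split is made at the sample median of 50 people. A negative r gives the same sizes with the sign reversed.

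**The case against.** The best defence is that the article promises little: the relevance of use will be explored, in a trial declared exploratory and unpowered. It does not say that high users will be set against all controls, nor that the result will be called a treatment effect. Since controls have no logins, a comparison within the e-IMR arm is a natural reading, and a condensed article may leave such detail to a fuller document. Covariates that include computer availability and literacy, diagnosis and relapse history could remove part of the confounding.

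Much of this stands, and it limits the point. It does not remove it. The article does state a method, sub-group analysis, and states it for use and baseline characteristics alike. A within-arm comparison is not a sub-group analysis of the treatment effect, and the text does not label it as an association. Covariate adjustment may reduce r, but it cannot supply controls with a level of use, and it does not deal with drop-out or with outcome driving use.

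Some stronger readings are tempting but unsupported:
- *That the result would be selection and nothing else.* A real effect of use may be present too. The two cannot be told apart.
- *That the bias must favour e-IMR.* Nothing in the article says that healthier or more motivated people log in more. Weekly prompts to register symptoms could make logins follow symptom burden, and the bias would then run the other way.
- *That the fidelity rating has the same defect.* It is taken at baseline as well as at twelve months, concerns a programme that both arms receive, and is not shown to be affected by arm. The article does not say which rating enters the analysis. Only the later one arises after randomisation.
- *That a decision on a definitive trial would be misled.* No section makes results by level of use a criterion for one.

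**Conclusion.** The point holds, at moderate severity. That use is measured after randomisation, exists in one arm only and is assigned to sub-group analysis all follows directly from the Data collection, Step 6 and Analyses sections. So does the conclusion that no randomised contrast by level of use can be formed, which needs no assumption about size.

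The size does rest on assumptions: no true effect, normally distributed use, a median split, and a residual correlation of 0.2 to 0.5 that the documents do not supply. On those terms the upper half of users would differ from all controls by about 0.16 to 0.40 SD. This shows the mechanism and is not an estimate for this trial; with r = 0 there is no bias. Neither the size nor the direction can be learned from the documents.

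The intention-to-treat analysis is untouched, and describing use remains a legitimate aim.

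**What to change.** Before the login data are analysed, amend the Analyses text as follows.

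1. Take frequency of use out of the sub-group list.
2. Report use within the e-IMR arm only, as an exploratory association with outcome, adjusted for the baseline measures and characteristics already planned as covariates, and stated to be non-causal.
3. Express use relative to time in the programme where the login data allow. This reduces the purely mechanical link with early drop-out. It does not remove self-selection.
4. Where fidelity is examined as a moderator of the treatment effect, use the baseline rating. The twelve-month rating can be reported descriptively.

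A complier-average analysis is not required. A use threshold would need the assumption that use below it has no effect, and with about 50 per arm, clustering and high expected attrition the estimate would be imprecise. Relating early use to later outcome would need time-stamped logins, which the article does not promise.

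The cost is a change of wording, with no data beyond those planned. The one loss is a weaker dose-response statement. Aim 3 is still served.

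### Sub-group analyses do not estimate whether the e-IMR effect differs by consumer, trainer or fidelity factors; interaction terms in the planned multilevel model would

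*Protocol article*

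**What the plan says.** The Analyses section of the protocol article plans multilevel regression with a random setting effect and repeated measures, adjusted for baseline measures and participant characteristics. It then says that the relevance of website use, "consumer characteristics, trainer characteristics, and IMR Fidelity Scale ratings will be explored by performing sub-group analyses".

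Data collection gives the lists behind these terms:

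- Consumer characteristics: "age, gender, living situation, social economic status, diagnosis, time since diagnosis, previous treatment", then "latest relapse, relapse frequencies in the past, and computer/internet availability and literacy". That is 10 items, or 11 if computer availability and literacy are counted separately.
- Trainer characteristics: "profession, highest education, gender, age, years of experience in mental health, and the number of executed IMR programmes in the past". That is 6 items.
- Fidelity is rated on trainers at baseline and at twelve months.
- There are seven outcome instruments if the clinician and consumer versions of the IMR scale are counted separately.

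Step 6 describes an "exploratory cluster randomized controlled trial with a twelve-month follow-up from baseline" and says that "we need 50 participants in both conditions", because high attrition is expected. It also says: "This trial will not be powered as it will aim to (1) explore the potential effectiveness and effect-size".

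**The concern.** A characteristic is relevant to the intervention if the e-IMR effect changes with it. That is a difference between two treatment effects. Separate results in each sub-group do not estimate that difference or give its uncertainty. They invite the reader to compare one significant result with one non-significant result, and with small strata such a pattern is common even when the effect is the same everywhere.

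Trainer characteristics and fidelity ratings raise a second issue. They vary between trainers, so their information is limited by the number of trainers or settings, which the article does not give. Sub-grouping participants on them overstates precision unless that level is modelled.

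What is at stake is the quality of the leads. An exploratory trial exists to produce leads, and a list of apparent works-here-but-not-there patterns would be hard to tell from noise.

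**Working it through.** **Inputs from the article.** 50 participants per condition, read as 100 in total (the wording could also mean 50 overall). Consumer factors 10 or 11, trainer factors 6, fidelity 1, so 17 or 18 without website use. Seven instruments. The article gives no alpha, effect size, SD, intracluster correlation or attrition rate, so the figure of 50 cannot be reproduced.

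**Assumptions.** Two-sided 5% level, a binary factor that splits the sample evenly, outcomes in SD units, and a true effect that is identical in both halves.

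**Standard errors for N analysed, before clustering.**

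- Overall effect: 2/√N. For N = 100 this is 0.20.
- Effect within one half: 2/√(N/2), which is √2 times the overall value. For N = 100 this is 0.283.
- Interaction (difference between halves): 4/√N, which is twice the overall value. For N = 100 this is 0.40.

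An overall standard error of 0.25 corresponds to N = (2/0.25)² = 64 without clustering, or to N = 100 with a design effect of (0.25/0.20)² = 1.56. The range 0.20 to 0.25 therefore runs from no attrition and no clustering to a moderate amount of either.

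**Chance that exactly one half is significant.** With power p in each half, p = Φ(d/s − 1.96) + Φ(−d/s − 1.96), where d is the true effect and s the standard error within one half. The chance is 2p(1 − p).

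| Overall SE | SE in one half | True effect | p | 2p(1 − p) |
|---|---|---|---|---|
| 0.25 | 0.354 | 0.3 | 0.136 | 23% |
| 0.20 | 0.283 | 0.3 | 0.186 | 30% |
| 0.25 | 0.354 | 0.5 | 0.293 | 41% |
| 0.20 | 0.283 | 0.5 | 0.424 | 49% |
| any | any | 0 | 0.050 | 9.5% |

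If 50 is the overall total, the overall standard error is 0.283, and the chances are 21% (0.3 SD) and 36% (0.5 SD).

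**Comparison with an interaction test.** When the effect is uniform, an interaction test is falsely positive 5% of the time, whatever the size of that effect. A simulation took N = 100, 18 independent binary factors, seven outcomes correlated 0.3 to 0.7, a uniform effect of 0.5 SD and no clustering. Out of 18 × 7 = 126 factor-outcome pairs, about 61 to 62 showed significance in exactly one half, and about 6 showed a significant interaction.

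**What interaction terms cannot do.** With a standard error of 0.40, the 95% interval is about ±1.96 × 0.40 = ±0.78 SD. The interaction detectable with 80% power is 1.12 SD, and power for an interaction of 0.5 SD is 24%. At N = 50 the standard error is 0.57 and that power is 14%.

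**The case against.** The strongest reply is that this is one sentence on secondary exploration in a condensed article. Which factors, cut-points and terms to use can be left to a full protocol or analysis plan that is not shown. The word sub-group does not exclude interaction terms, and the multilevel model in the same paragraph could hold them. The trial is openly exploratory and unpowered.

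Much of this stands, and it rules out several stronger readings:

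- A reader might infer that 126 tests at 5% are planned. The article states no alpha, no significance test for sub-groups and no full crossing of factors with instruments.
- A reader might cite 126 × 0.05 = 6.3 expected false positives against the method. That figure reflects the length of the list. Interaction tests over the same list would give the same 6.3.
- A reader might infer that the results would steer targeting of a later trial or of implementation. None of the four aims in Step 6 is a claim about who benefits, and the article gives sub-group results no such use.
- A fixed cap on the number of factors is a preference in an exploratory trial. Three factors on seven instruments still make 21 tests and 21 × 0.05 = 1.05 expected false positives.

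The reply does not remove the core. The sentence names a method, and on its ordinary reading that method does not answer the question of relevance. Leaving details to another document does not alter that. Calling the work exploratory does not make a comparison of two p-values informative.

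**Conclusion.** The concern holds in a limited form. Read as separate sub-group results, the stated method does not estimate effect modification and is likely, though not certain, to yield spurious contrasts. The size is a 23% to 49% chance per factor and outcome that a uniform effect of 0.3 to 0.5 SD is significant in exactly one half, against 5% for an interaction test. With no effect at all the chance is 9.5%. These figures rest on an assumed 5% level, an even split and an overall standard error of 0.20 to 0.25 SD. None of these is in the article, and the effect sizes are assumed too.

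This is a matter of choosing a better and cheap method. It is not an error in a stated figure. The article should be changed or clarified on this point, but the trial's exploratory aims are not invalidated.

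**What to change.** Reword the sentence in the Analyses section along these lines:

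- Explore baseline consumer characteristics, trainer characteristics and baseline fidelity through treatment-by-characteristic interaction terms in the full-sample multilevel model. Enter trainer and fidelity factors at trainer or setting level.
- Report each as an estimate with a 95% confidence interval, state how many were examined, and label all of them hypothesis-generating.
- Preferably name a short list of priority factors and one or two outcomes before the data are opened.
- Analyse website use separately and descriptively within the e-IMR arm. Controls have only the textbook and use is measured after randomisation, so no treatment-by-use interaction can be estimated. The twelve-month fidelity rating is also measured after randomisation and should not serve as a baseline modifier.

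The cost is wording, slightly more modelling work and fewer sub-group statements. No new data are needed. The change makes the comparison valid but does not make any single interaction precise.
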